### Field procedures

Community sensitisation activities take place to inform target communities of the study’s aims and promote voluntary participation. Different support materials are used. Some of these include local drama groups, information brochures and an FGS manual edited by Zambart. Study community workers (SCWs) register expressions of interest and conduct home visits within the randomised zones to women that have expressed interest in participating in the study. All SCWs are females. Every participant has a total of three visits during the study: baseline, 12 and 24 months from recruitment. A schematic study flow is shown in figure 1.

**Figure 1 F1:**
[figure not shown]
Schista study flow. CAA, circulating anodic antigen; HPV, human papillomavirus; STIs, sexually transmitted infections.

#### Home visits

Home visits are conducted by SCWs who perform a demonstration of self-sampling, using a 3D model for illustration (online supplemental figure 1). SCWs also obtain consent from participants and administer demographic and exposure questionnaires. After obtaining informed consent and completing questionnaires on demography, clinical symptoms and other relevant health and water contact information, the SCWs offer participants two genital self-swabs. The first swab is stored in PrimeStore MTM molecular transport media (donated by Longhorn Vaccines and Diagnostics, Bethesda, Maryland, USA) for the detection of *Sh* by molecular methods (PCR and RPA). The second swab is stored in Cytopreserve for HR-HPV detection by Xpert.^27^ Participants are also offered two commercial self-tests: one oral (saliva) for HIV^28^ and one vaginal self-swab for *Tv*.^29^ For both self-tests, results are read by the SCW and given immediately to the participant. After all the self-sampling swabs are delivered, the SCW record acceptability results based on a Likert Scale. A confirmatory test is performed on site if there is a positive self-test for HIV. All HIV-positive women are referred to the local clinic for further management and linkage to care. For *Tv*, women are referred for treatment at the clinic visit. A urine sample is analysed via microscopy for *Sh* ova detection and circulating anodic antigen (CAA).^30^

10.1136/bmjopen-2023-080395.supp1Supplementary data

#### Biopsy procedure

Women testing positive for any HR HPV by PCR (Xpert HPV) during the home visit and depending on their age and HIV status (see below) are referred for colposcopy. Visual inspection using acetic acid and lugol’s iodine (VIA/VILI) is performed by a trained gynaecologist before biopsy of visible lesions. If no lesions are visible, two random biopsies are taken from normal areas including the transformation zone (at 12 and 6 o’clock) (figure 2). Cervical biopsies will be processed at the pathology laboratory at National Health laboratory Service, Johannesburg, South Africa and read using the two-tier CIN classification system.

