## Methods and design

### Study design

The Zipime Weka Schista (Do self-testing sister!) study is a longitudinal cohort designed as a holistic approach to FGS detection at scale in the community. The study design will test the hypothesis that integration of home self-sampling for the screening of FGS in conjunction with HR-HPV and self-testing for HIV and STIs is a diagnostically accurate, cost-effective and self-empowering strategy that will increase the detection of cases and improve access to care for women of reproductive age in SSA.

The two main aims of the Zipime Weka Schista study are:

To assess the performance of genital self-sampling, compared with healthcare provider sampling obtained for the detection of *Sh* by molecular testing (real-time PCR and recombinase polymerase assay (RPA)) across two different *Sh* endemicity settings in Zambia.To assess the observed costs of integrating community-based multiple pathogen genital self-sampling (*Sh*, HPV, STIs) and oral self-test (HIV) into a one-stop home intervention and project costs at scale.

Our secondary aims are to explore the epidemiological and immunological interrelationships between FGS and HPV as a potential risk factor for cervical cancer and expand knowledge on HIV acquisition in the presence of coinfections. We will also measure acceptability and feasibility of home-based multiple genital self-sampling and to measure HIV linkage to care and cervical cancer management after home self-sampling and testing. We will further aim to evaluate the effect of FGS and other STI on the diagnostic accuracy of visual inspection for the detection of cervical precancer (CIN2+, CIN3+) and to describe the association of FGS, HPV, HIV and STIs with the presence concentration, diversity and relative abundance of other key cervicovaginal microbiota and infections. We will also aim to consolidate testing for FGS and HPV into one field-applicable multiplex molecular assay and to recruit a subset of male household members of recruited participants screening male genital schistosomiasis.

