#### Women diagnosed with cervical precancer and invasive cervical cancer

If found to have histopathology verified CIN2+, participants are recalled for CIN2+management. This visit is scheduled at the earliest convenient date once the result is known. In Zambia, all patients with cancer are referred to the Cancer Diseases Hospital (CDH) based in Lusaka. Patients are filtered through the district and provincial hospitals serving as primary centres for cervical cancer screening countrywide before being referred to CDH for definitive treatment. Treatment at CDH is done according to the nationally and globally developed guidelines.^36^

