### Statistical analysis

To assess the performance of genital self-sampling compared with healthcare provider sampling for the detection of *Sh,* sensitivity, specificity, positive predictive value (PPV) and negative predictive value (NPV) will be calculated together with 95% CIs. Results will be presented overall and stratified by geographical setting. To explore associations of baseline FGS with the prevalence of cervical precancer at baseline and cervical precancer incidence at 12 and 24 months, logistic regression will be used to estimate ORs. Associations between baseline FGS and HR-HPV persistence at 12 months will be estimated with generalised estimating equation to account for multiple HR-HPV infection and multiple infection states (persistence and clearance).^46^ The association of FGS with HIV acquisition will be assessed using Poisson regression, controlling for key confounders.

Other outcome measures obtained in the study will include (1) HIV incidence rate, HR-HPV clearance and persistence, prevalence and incidence of cervical precancer (histology confirmed CIN2 or CIN3+), measures of association between different exposures (reproductive tract infections); (2) acceptability of multiple genital self-sampling interventions; (3) rates of antiretroviral initiation, continuation of treatment and access to care; (4) cervical precancer diagnosis and treatment, testing and management of STIs; (5) the presence or absence of cervicovaginal microbiota in women with FGS, HPV and STIs. Expressed as relative abundance (percentage abundance of each species), genomic concentration per micro-organism (genome equivalents per mL) and (6) sensitivity, specificity, PPV, NPV of visual inspection of the cervix according to FGS status and integrated molecular field-applicable testing platform for *Sh* and HR-HPV.

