#### Economic analysis

A full economic costing from a provider’s and patient’s perspective is ongoing alongside data collection. Cost data are collected by combining a bottom-up and top-down approach following established costing guidelines,^47^ and STI self-testing economic evaluations in the region. This allows us to estimate the total intervention cost, and unit costs per woman screened, FGS infection detected, per case of CIN2+ detected, per person linked to care, per person successfully treated overall and per pathogen identified. We will model the costs across a set of scale-up scenarios to understand the budget implications of introducing widescale self-screening. Populating a health economics decision model with the study outcomes, we will identify cost thresholds under which joint self-sampling for FGS, HPV, STIs and HIV is cost-effective. This will be relevant for informing the maximum threshold diagnostic kit price based on its potential cost-effectiveness.^48^ MoH and policy-makers will be informed on the most cost-effective screening strategy to implement for FGS screening. This study constitutes the first economic evaluation of FGS.

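### Biopsies are read on a two-tier CIN scale, but a secondary aim needs visual-inspection accuracy at both CIN2+ and CIN3+, and on the ordinary reading CIN3+ cannot be derived

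*Protocol article*

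**What the plan says.** **Reading scale.** The Biopsy procedure section sends the biopsies to an external pathology laboratory, where they are to be "read using the two-tier CIN classification system". The two tiers are not defined, and no further grading is described.

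**Thresholds wanted.** Among the secondary aims, the Study design section includes the effect of FGS and other STIs on the "diagnostic accuracy of visual inspection for the detection of cervical precancer (CIN2+, CIN3" (the bracket closes with a plus sign, so the second threshold is CIN3+). The Statistical analysis section lists "prevalence and incidence of cervical precancer (histology confirmed CIN2 or CIN3" (again CIN3+). Later in the same list it gives "sensitivity, specificity, PPV, NPV of visual inspection of the cervix according to FGS status", without repeating a histology threshold.

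**Threshold used elsewhere.** The section on women diagnosed with precancer and invasive cancer states: "If found to have histopathology verified CIN2+, participants are recalled for CIN2+management". The Economic analysis section plans a unit cost "per case of CIN2+ detected". Both use CIN2+ only.

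**The concern.** A scale that sorts results into low grade and high grade has a single cut. The secondary aim asks for two. If the laboratory returns only the tier, a woman with CIN2 and a woman with CIN3 look the same in the dataset, and no later analysis can separate them.

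At stake is the accuracy of visual inspection at CIN3+, one of the two thresholds that the aim names. CIN3+ prevalence and incidence would go with it if the outcome list is meant grade by grade. Timing matters because the slides are read outside the study team, and the article already lists limited histopathology capacity as a source of delay. A second reading later would be harder to arrange than one extra item on the report now.

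**Working it through.** No sample size, power or event figure enters this point, so there is no stated figure to reproduce. The check is logical.

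**Step 1. Cuts needed.** A scale with *k* ordered groups has *k* − 1 cuts. CIN2+ and CIN3+ are two nested thresholds, so *k* − 1 must be at least 2 and *k* at least 3: below CIN2, CIN2, and CIN3 or worse.

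**Step 2. Cuts available.** Two tiers give 2 − 1 = 1 cut.

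**Step 3. Where the cut could lie.**

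| Meaning of the two tiers | CIN2+ | CIN3+ | Fits recall and costing at CIN2+? |
|---|---|---|---|
| Low versus high grade, cut at CIN2 | derivable | not derivable | yes |
| Cut at CIN3 | not derivable | derivable | no |
| CIN2 versus CIN3+, everything lower called negative | derivable | derivable | yes, but this is really three groups |
| Any tiers, with the CIN grade also recorded | derivable | derivable | yes |

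The first row is the ordinary meaning of the term. It is also the only true one-cut reading that agrees with the recall rule and the unit cost. Under it the CIN3+ half of the secondary aim fails. The last two rows would remove the problem, but the article states neither.

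**Step 4. Do normal and invasive results help?** The laboratory must also be able to report normal tissue, because random biopsies are taken when no lesion is visible, and invasive cancer, which the article handles separately. The output is then normal, low grade, high grade and invasive: 4 − 1 = 3 cuts. One lies below low grade, one between low and high grade, and one above high grade. None falls between CIN2 and CIN3. CIN2+ is high grade plus invasive. CIN3+ would still require the high-grade group to be split.

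**Step 5. Which outcomes depend on the split.**
- Accuracy of visual inspection at CIN3+ (Study design): yes, by name.
- Prevalence and incidence of precancer (Statistical analysis): only if CIN2 and CIN3+ are to be reported separately. Taken as one composite, CIN2 or CIN3+ is the same as CIN2+ and needs no split.
- Logistic regression of precancer on baseline FGS (Statistical analysis): no. The outcome is precancer without a CIN3+ version, and it can run on CIN2+.
- Recall and unit cost: no. Both use CIN2+.
- Self-sampling performance for *S. haematobium*, the sample size and the costs: no. The first two do not use histology, and the costing uses only CIN2+.

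**The case against.** The best case on the other side has three parts.

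**The tiers are undefined and the source is a condensed article.** The content of a pathology report form is the kind of detail that a full protocol holds, and the flow chart for precancer determination (Figure 2) is not shown. The laboratory may well record the grade. This stands as a limit: the conclusion is conditional on the ordinary meaning of two-tier. It does not dispose of the point. The article positively states a reading scale and positively states a threshold that this scale, ordinarily understood, does not give. That is a conflict between two statements, not a gap.

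**Two tiers cannot be the whole output**, since normal and invasive results must be reportable. That is correct, but as shown above those extra categories do not separate CIN2 from CIN3.

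**Little hangs on it.** Much of this stands. The explicit evidence is one parenthesis in a secondary aim. The outcome list can be read as a composite, and the accuracy item in the analysis section names no threshold.

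A reader might be tempted to go further and infer that every CIN3+ result is irretrievably lost when the slides are read, or that a planned analysis of FGS against CIN3+ fails. The documents support neither. They do not say that the grade goes unrecorded, and existing reports may state it. They name no FGS model with CIN3+ as its outcome.

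**Conclusion.** The concern holds in a limited form. The reading scale fixed under Biopsy procedure and the two thresholds named under Study design do not fit together. With low-grade/high-grade tiers and the cut at CIN2, visual-inspection accuracy at CIN2+ can be reported and accuracy at CIN3+ cannot.

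This rests on two assumptions: that two-tier has its ordinary meaning, and that the laboratory returns the tier without the CIN grade. If either is wrong, both thresholds can be derived and only the wording needs repair. The further effect on CIN3+ prevalence and incidence needs a third assumption, that the outcome list means separate grades.

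The size cannot be put as a number, because the article does not say how many high-grade results are expected or how they divide between CIN2 and CIN3. The issue is moderate. It touches part of the secondary outcomes and does not threaten the main aims, so it would be too strong to treat it as a defect that must be cured before the study can answer its principal questions.

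**What to change.** Under Biopsy procedure, define the two tiers. Then do one of the following.

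1. **Keep CIN3+.** Have the laboratory record the CIN grade (CIN2 versus CIN3 or worse) for each biopsy beside the tier. For biopsies already read, take the grade from the existing report where it is stated, and count how many reports do not state it. The cost is one extra field on the report and a look back through completed reports, with no new procedure for participants.
2. **Drop CIN3+.** Restrict the histology outcomes under Study design and Statistical analysis to CIN2+. The cost is an edit to the text and the loss of the CIN3+ threshold from the secondary aim.

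In either case, reword the outcome list under Statistical analysis so that it is clear whether CIN2 and CIN3+ form one composite or two separately reported outcomes.

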**Figure 2 F2:**
[figure not shown]
Flow chart for cervical precancer determination in HIV negative an women living with HIV (WLHIV). *HR-HPV detected using Xpert; **HR-HPV positive WLHIV aged 20 years and older and HIV-negative women aged 25 years and older only. HR-HPV, high-risk human papillomavirus.

HIV-negative women under the age of 25 and women living with HIV under the age of 20 years have all procedures performed, including HPV testing in the community, but they do not undergo biopsy in clinic despite positive HR-HPV results.^34^ This strategy follows ethical concerns of unnecessary biopsy and management of cervical lesions based on known HPV clearance and low risk of cervical precancer in young women.^35^ For these women, there is annual longitudinal follow-up for 2 years with repeated infection and clinical reassessments.

#### Women diagnosed with cervical precancer and invasive cervical cancer

If found to have histopathology verified CIN2+, participants are recalled for CIN2+management. This visit is scheduled at the earliest convenient date once the result is known. In Zambia, all patients with cancer are referred to the Cancer Diseases Hospital (CDH) based in Lusaka. Patients are filtered through the district and provincial hospitals serving as primary centres for cervical cancer screening countrywide before being referred to CDH for definitive treatment. Treatment at CDH is done according to the nationally and globally developed guidelines.^36^

### Laboratory procedures

The collection, storage and processing of all study samples are summarised in table 1. Urine samples are processed for (1) urine parasitology: approximately 10 mL (minimum) of urine is processed by centrifugation to detect Sh eggs by microscopy performed at the local government clinics in Kafue and Livingstone in Zambia by a trained technician and (2) CAA antigen assay: a 2 mL of urine is stored at 4°C and shipped to Lusaka and further to Leiden University Medical Center, The Netherlands.^37^

**Table 1 T1:** Sample storage and processing for the Schista study

Sample	Location	Storage	Sample processing	Location of processing
Self-collected swab Provider-collected swab	Home	Room temperature (Stored in Primestore media)	Sh DNA (PCR, RPA) GeneXpert- High Risk HPV DNA*	Zambart (Zambia)
Urine for microscopy	Home	Room temperature	Sh eggs Urine haemastix	District Laboratory (Kafue, Livingstone, Zambia)
Urine stored for CAA	Clinic	4°C	Circulating Anodic Antigen	Leiden University Medical Centre (The Netherlands)
Cervicovaginal lavage	Clinic	−20°C	Sh DNA (PCR, RPA) GeneXpert- CT/NG Microbiota	Zambart (Zambia)
Blood for serology	Clinic	−20°C	Sh, STI antibody	Zambart (Zambia)
Colposcopy images	Clinic	Encrypted server	Expert review computer analysis	Zambia London School of Hygien and Tropical Medicine (UK)

*High-risk HPV by self-collected swab only.

CAA, circulating anodic antigen; HPV, human papillomavirus; RPA, recombinase polymerase assay; *Sh*, *Schistosoma haematobium*; STIs, sexually transmitted infections.

All genital samples (home/clinic) are processed for (1) Detection of schistosoma DNA using ITS-2 real-time PCR processed at Zambart laboratories in Lusaka, Zambia.^31 38^ From the DNA already extracted for PCR additional well-validated qPCR assays will be used^39^ to characterise the vaginal microbiota by quantifying key species and (2) Detection of Schistosoma DNA using RPA. Up to 2 mL of fluid from vaginal lavage is stored at −20°C and shipped to Lusaka. This assay is processed at Zambart laboratory in Zambia^40 41^ and (3) Inflammatory Markers. Up to 3 mL of fluid from vaginal lavage is stored at −80°C and shipped to Lusaka.^25 31 42^

### Development of a multiplex assay for *Sh* and HR-HPV testing

In a exploratory study, we will aim to integrate into one molecular assay the RPA for *Sh* and HPV to increase accessibility and feasibility of molecular dual pathogen screenings after encouraging results on the validaty of the CVL RPA assay against standard real-time PCR,^43^ which could be coupled with oncogenic HPV genotypes.^44^

### Qualitative assessment

#### In-depth feasibility and acceptability of integrated sampling, testing and treatment

Previous work has documented the acceptability of performing multiple genital swabs at a single encounter.^27^ For the current proposal, in-depth cognitive interviews will be delivered to a subset of participants to evaluate the acceptability of the multipathogen self-swabbing strategy (three genital swabs and one oral swab).^45^

### Statistical analysis

To assess the performance of genital self-sampling compared with healthcare provider sampling for the detection of *Sh,* sensitivity, specificity, positive predictive value (PPV) and negative predictive value (NPV) will be calculated together with 95% CIs. Results will be presented overall and stratified by geographical setting. To explore associations of baseline FGS with the prevalence of cervical precancer at baseline and cervical precancer incidence at 12 and 24 months, logistic regression will be used to estimate ORs. Associations between baseline FGS and HR-HPV persistence at 12 months will be estimated with generalised estimating equation to account for multiple HR-HPV infection and multiple infection states (persistence and clearance).^46^ The association of FGS with HIV acquisition will be assessed using Poisson regression, controlling for key confounders.

Other outcome measures obtained in the study will include (1) HIV incidence rate, HR-HPV clearance and persistence, prevalence and incidence of cervical precancer (histology confirmed CIN2 or CIN3+), measures of association between different exposures (reproductive tract infections); (2) acceptability of multiple genital self-sampling interventions; (3) rates of antiretroviral initiation, continuation of treatment and access to care; (4) cervical precancer diagnosis and treatment, testing and management of STIs; (5) the presence or absence of cervicovaginal microbiota in women with FGS, HPV and STIs. Expressed as relative abundance (percentage abundance of each species), genomic concentration per micro-organism (genome equivalents per mL) and (6) sensitivity, specificity, PPV, NPV of visual inspection of the cervix according to FGS status and integrated molecular field-applicable testing platform for *Sh* and HR-HPV.

#### Quality control

Several procedures have been employed to ensure the quality of the study data, maximising the validity and reliability of the data obtained and of the evaluation of the results: These include the following (a) 10% of all samples (positive and negative results from diagnostic assays) will be reviewed blindly by experts at different institutions; parasitology (Liverpool School of Tropical Medicine, Liverpool, UK), PCR (Natural History Museum, London, UK), colposcopic images (University of Zambia, Lusaka, Zambia).

#### Economic analysis

A full economic costing from a provider’s and patient’s perspective is ongoing alongside data collection. Cost data are collected by combining a bottom-up and top-down approach following established costing guidelines,^47^ and STI self-testing economic evaluations in the region. This allows us to estimate the total intervention cost, and unit costs per woman screened, FGS infection detected, per case of CIN2+ detected, per person linked to care, per person successfully treated overall and per pathogen identified. We will model the costs across a set of scale-up scenarios to understand the budget implications of introducing widescale self-screening. Populating a health economics decision model with the study outcomes, we will identify cost thresholds under which joint self-sampling for FGS, HPV, STIs and HIV is cost-effective. This will be relevant for informing the maximum threshold diagnostic kit price based on its potential cost-effectiveness.^48^ MoH and policy-makers will be informed on the most cost-effective screening strategy to implement for FGS screening. This study constitutes the first economic evaluation of FGS.

